### Primary outcome: feasibility to deliver the protocol as designed

Feasibility will be determined by measures of the recruitment process, intervention fidelity and outcome measurement completeness, specifically,

Study accrual rates: a minimum of 30% of eligible patients or one to two patients per site per month are enrolled.Protocol adherence: 75% of patients commencing intervention within 72 hours of ICU admission, minimum of 70% of planned interventions delivered.Blinded outcome assessment: functional assessment performed at three time points in 80% of survivors by physiotherapists working within the hospital but not within the ICU.

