**Methods and analysis:**

90 acute care medical patients from two mixed medical–surgical ICUs will be recruited. We will include ventilated patients within 72 hours of initiation of mechanical ventilation and expected to be ventilated a further 48 hours or more. Patients will receive usual care or usual care plus two 30 min rehabilitation sessions 5 days/week.

Feasibility outcomes are (1) recruitment of one to two patients per month per site; (2) protocol fidelity with >75% of patients commencing interventions within 72 hours of mechanical ventilation, with >70% interventions delivered; and (3) blinded outcome measures recorded at three time points in >80% of patients. Secondary outcomes are (1) strength and function, the Physical Function ICU Test–scored measured on ICU discharge; (2) hospital length of stay; and (3) mental health and physical ability at 3 months using the WHO Disability Assessment Schedule 2. An economic analysis using hospital health services data reported with an embedded health economic study will collect and assess economic and quality of life data including the Hospital Anxiety and Depression Scales core, the Euroqol-5 Dimension-5 Level and the Impact of Event Score.

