### Objectives

Feasibility will be determined by measures of the recruitment process, intervention fidelity and outcome measurement completeness, specifically, (1) study accrual rates: a minimum of 30% of eligible patients or one to two patients per site per month are enrolled; (2) protocol adherence: 75% of patients commencing intervention within 72 hours of ICU admission, with a minimum of 70% of planned interventions delivered; and (3) blinded outcome assessment: functional assessment performed at three time points in 80% of survivors. The results will inform a larger fully powered RCT.

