### Participants

Ninety patients will be recruited. Eligible patients will be over 42 years old and will have an acute/unplanned medical admission to the ICU. They will be functionally independent prior to ICU admission (Barthel Index>80), in the hospital for <5 days prior to intubation and ventilation, intubated and ventilated for <72 hours, and expected to remain ventilated for a further 48 hours. Patients will be excluded if they are in the hospital for 5 days or more prior to ICU admission, have acute brain or spinal cord injury, known or suspected neurological/muscular impairment, condition limiting use of cycle ergometry (eg, lower limb fracture/amputation), not expected to survive >48 hours decided by consulting an intensivist and persistent therapy exemptions in the first 3 days of mechanical ventilation. Figure 1 presents the planned flow of patients through the study.

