### Interventions

All patients will receive usual medical, nursing and physiotherapy care while in intensive care. Each bedside nurse will be asked at the start of the shift if they have been involved caring for a patient in the intervention arm of the study. The ICU physiotherapy team, who are not involved with the delivery of the study delivery, will deliver all usual physiotherapy interventions in both groups. The physiotherapist delivering usual care will be asked to verify if they have delivered any of the study interventions. In the intervention arm, the protocolised physiotherapy programme will commence within 72 hours of ICU admission or as soon as possible thereafter and will continue for 28 days or until ICU discharge, whichever occurs first. Patients’ respiratory support can range from full mandatory ventilation through to oxygen supplementation with no mechanical support following extubation. Sedation is targeted throughout the time that the patient is intubated, and the ventilation mode is adjusted to patients’ needs, compliance and comfort at discretion at the start of each physiotherapy intervention, the participants’ level of sedation will be assessed using the Richmond Agitation–Sedation Scale (RASS)^53 54^ and the Confusion Assessment Method for ICU^55^will be undertaken. RASS will be targeted to a RASS between −1 and +1 by the bedside nurse. After 28 days of ICU admission, all patients will receive usual care physiotherapy interventions.

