### Group 2: Protocolised rehabilitation pathway

Patients will have usual care physiotherapy, in addition to the two protocolised intervention within 72 hours of ICU admission or as soon as possible thereafter. Patients will be screened for safety criteria to withhold the intervention prior to each planned intervention session (table 1).

**Table 1 T1:** Safety criteria for delivery of physical therapy interventions

	Criteria to commence physiotherapy	Criteria to stop/withhold physiotherapy intervention
Blood pressure	Mean Arterial Blood Pressure (MAP) 60–100 mm Hg, no change in vasopressor dose requirement for preceding 2 hours	Catecholamine-resistant hypotension with MAP <60 mm Hg
Heart rate	Between 40 and 140 beats/min	<50 or >140 beats/min
Respiratory rate	Sustained <40 breaths/min	Sustained >40 breaths/min
Temperature		>40°C
Oxygen requirement	If Fraction inspired oxygen (FiO_2_)>0.8 for passive exercise only	
	FiO_2_ <0.8 and (Positive End Expiratory Pressure) PEEP <15 cmH_2_O	
Desaturation		Sats fall <85% for>1 min
Other		Fall. Unplanned extubation. Acute bleeding. New-onset arrhythmia. Signs/symptoms of acute myocardial ischaemia. Patient pain/distress. Clinical team decides therapy intervention not appropriate. Refusal by patient or representative.

Those meeting criteria to withhold interventions will have issues addressed and reassessed for interventions 2 hours later. The two additional rehabilitation sessions will be delivered by the research physiotherapy staff including a therapy technician. This will comprise two mobility sessions the modality of the first, chosen at the discretion of the physiotherapist. The second session will be 30 min of supine cycling delivered in the afternoon.

The first rehabilitation intervention each day will be delivered in the morning. Planned interventions include passive or active range of movements, passive cycling, active cycling, in-bed exercises, sitting, mobilisation out of bed and walking. Daily assessment of the patient will be made to ensure the highest level of activity possible is provided for each individual patient given safety considerations and capability of the patient.

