## Discussion

EMPRESS is a feasibility study to assess if an RCT of protocolised rehabilitation with supine cycling can be delivered in ventilated patients in ICUs with differing organisational structures with blinded follow-up assessments. A recent meta-analysis indicated that protocolised rehabilitation significantly reduces duration of mechanical ventilation and ICU length of stay.^23^ This is consistent with our findings when we introduced the early rehabilitation programme outlined here in our ICU.^45^ Passive cycling commenced on ventilated patients may assist the recovery muscle strength in ICU patients,^43^ although the overall benefits of leg cycle ergometry in the critically ill is inconclusive.^44^ We describe a protocolised rehabilitation programme with supine cycling delivered as close to intubation as possible, at an intensity according to the patients’ highest performance capability.

Both patient and organisational issues are recognised to the delivery of early rehabilitation of the critically ill patients.^35^ A frequently reported challenge is the lack of appropriately qualified staff.^80^ This study evaluates the safety, feasibility, effectiveness of delivery and cost efficiency of using therapy technicians to deliver protocolised rehabilitation interventions. In addition to the clinical benefits, early physical rehabilitation can also be cost saving.^49^ Even with the cost of employment of additional therapy technicians specifically to assist in the delivery of we have found this early rehabilitation programme cost effective.^81^

This study will collect data on the dose of intervention delivered to all patients, reasons for non-delivery of protocol interventions, and the level of experience of therapists delivering the interventions. A qualitative process evaluation is designed to identify both patient and organisational challenges that have potential to be addressed in a potential future study. Findings will inform refinement of trial design and evaluation of the intervention, clarifying causal mechanisms behind study outcomes and providing additional context not adequately captured by the quantitative data. The process evaluation will be consistent with Medical Research Council guidance for conducting process evaluations of complex healthcare interventions.^82^

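### The 72-hour start criterion runs from ICU admission while eligibility runs from ventilation, so some validly enrolled patients have failed it before randomisation

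*Protocol article*

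**What the plan says.** The article uses two starting points for one 72-hour period.

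**From ICU admission**
- Primary outcome section: "75% of patients commencing intervention within 72 hours of ICU admission".
- Objectives: "75% of patients commencing intervention within 72 hours of ICU admission, with a minimum of 70% of planned interventions delivered".
- Interventions, as a delivery instruction: "the protocolised physiotherapy programme will commence within 72 hours of ICU admission or as soon as possible thereafter".
- Group 2 (Protocolised rehabilitation pathway) repeats that instruction with the same allowance for a later start.

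**From mechanical ventilation**
- Abstract (Methods and analysis), for the same criterion: "protocol fidelity with >75% of patients commencing interventions within 72 hours of mechanical ventilation".
- Participants, as an eligibility rule: "in the hospital for <5 days prior to intubation and ventilation, intubated and ventilated for <72 hours". The Abstract's inclusion rule also counts from the start of ventilation.
- The Participants exclusion for persistent therapy exemptions covers the first 3 days of ventilation.

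The Discussion describes the programme as "supine cycling delivered as close to intubation as possible", which fits the ventilation clock.

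Time before intubation is limited only by the rule of under 5 days in hospital. No separate limit applies to time in the ICU before intubation.

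**The concern.** There are two linked problems. First, a primary feasibility criterion has two definitions, so the same data can give two different rates against one threshold. Second, the definition in the outcome section does not fit the eligibility rule. Entry is judged by hours of ventilation and success by hours since ICU admission. Where intubation follows ICU admission, a patient can still be eligible after the success deadline has passed.

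Such a patient counts as a failure of intervention delivery although the therapy team had no chance to succeed. The rate is meant to inform a larger trial. A low rate caused by late enrolment calls for a different remedy (earlier screening and consent) from one caused by poor delivery (staffing and training), and the criterion as written cannot tell them apart.

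**Working it through.** **Inputs from the article**
- Deadline: 72 h from ICU admission (Objectives; Primary outcome) or from mechanical ventilation (Abstract).
- Eligibility: ventilated under 72 h, and under 5 days (120 h) in hospital before intubation (Participants).
- 90 patients (Sample size calculation), randomised 1:1 (Study design).
- Threshold: 75%.

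The article gives no precision figure for this criterion. Its stated half-widths (±5.2%, ±7.3%, ±9.5%) concern recruitment and mortality; they reproduce but do not bear on this point.

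**Step 1. Intubation after ICU admission.** Let *g* be the hours from ICU admission to intubation.
- The ICU-clock deadline falls at 72 − *g* hours of ventilation.
- Eligibility lasts until 72 hours of ventilation, which is *g* + 72 hours after ICU admission.
- The last *g* hours of the eligibility window therefore lie past the deadline, a share of *g*/72.

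| *g* (illustrative) | Deadline, in hours of ventilation | Latest valid enrolment after ICU admission | Share of window past deadline |
|---|---|---|---|
| 6 h | 66 h | under 78 h | 6/72 = 8% |
| 12 h | 60 h | under 84 h | 12/72 = 17% |
| 24 h | 48 h | under 96 h | 24/72 = 33% |
| 48 h | 24 h | under 120 h | 48/72 = 67% |

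The last column is a share of hours, not of patients.

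Example: *g* = 24 h, enrolled at 60 h of ventilation. Time since ICU admission is 24 + 60 = 84 h, so the outcome-section deadline passed 12 h earlier. On the Abstract's clock 72 − 60 = 12 h remain.

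**Step 2. Ventilation before ICU admission.** Let *v* be the hours ventilated before ICU admission. The ICU clock accepts a start up to 72 + *v* hours of ventilation (78 h for *v* = 6); the Abstract's clock stops at 72 h. Misclassification therefore runs in both directions.

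**Step 3. Margin at the threshold.** Assume the criterion is scored in the intervention arm, with 90/2 = 45 patients.
- Required: 0.75 × 45 = 33.75, so 34 must start on time and at most 11 may miss.
- 34/45 = 75.6% (Wilson 95% CI 61.3% to 85.8%).
- 33/45 = 73.3% (Wilson 95% CI 59.0% to 84.0%).

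If exactly 34 start on time on one clock, one patient classified differently on the other takes the rate below 75%.

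**Step 4. Sensitivity, on assumptions not in the article.** Suppose 85% of patients who can still be on time do start on time, and a fraction *f* are enrolled after the ICU clock has run out. The on-time probability is 0.85 × (1 − *f*), and the chance of reaching 34 of 45 is a binomial tail.

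| *f* | On-time probability | Chance of at least 34/45 |
|---|---|---|
| 0% | 0.850 | 0.97 |
| 10% | 0.765 | 0.64 |
| 20% | 0.680 | 0.18 |
| 30% | 0.595 | 0.02 |

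This shows how sensitive the criterion is; it does not estimate *f*.

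**The case against.** The strongest reply is that the body of the article is consistent. Objectives, Interventions, Group 2 and Primary outcome all use ICU admission, and only the Abstract's version of the criterion departs from them. On that view the error is one phrase in a summary. The rationale also speaks in places of rehabilitation early after ICU admission, so the Discussion's remark about intubation does not settle intent. Correcting the Abstract would indeed remove the contradiction, but it would confirm the ICU clock, which is the one that does not fit the eligibility rule. Valid enrolments would still arrive already failed.

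A second reply is that the protocol tolerates late starts, reports deviations and collects reasons for non-delivery. This stands in part: a late start is not a treatment violation, and its cause could be traced afterwards. But the allowance for starting as soon as possible after 72 hours appears only in the delivery instructions. It is absent from the criterion in Objectives and Primary outcome, so a late start still scores as a failure.

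A third reply is that the size is not established, and this stands. The share of patients with a gap is not given, and *g*/72 would become a failure rate only if enrolment were spread evenly over the window. Assent is sought within 6 hours of confirmed eligibility, which limits consent delay, although it does not fix when eligibility is confirmed. The 34-to-33 example sits on the threshold by construction, and a shift of one patient (2.2 points) is small against the interval.

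**Conclusion.** The concern holds. One primary feasibility criterion has two time origins, and the one in the outcome section is incompatible with the eligibility rule for some patients intubated after ICU admission. This follows from the text and needs no assumption.

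The practical size is unknown. It depends on how many patients have a gap between ICU admission and intubation, how long the gap is, and how late in the window they are enrolled. The figure of 45 assumes equal arms and scoring in the intervention arm only. The 85% on-time rate and the 10% to 30% late shares are illustrative. Where intubation and ICU admission coincide, the two clocks agree.

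The article makes no stop decision on this criterion alone, and feasibility rates are to be reported with 95% CIs. The consequence is therefore a fidelity estimate that may be misread, not an invalid trial. It should be corrected because it changes how a primary threshold is scored.

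**What to change.** Use start of mechanical ventilation as the single time origin in the Abstract, Objectives, Interventions, Group 2 and Primary outcome. It matches eligibility, the therapy-exemption exclusion and the intent stated in the Discussion. Every patient is then still inside the 72 hours at enrolment.

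Report alongside the criterion:
- time from randomisation to first session;
- the number of patients whose 72 hours had already run out at randomisation, or would run out before the next weekday session, since delivery is Monday to Friday only.

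These separate late enrolment from non-delivery.

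The cost is a wording change, a little more reporting and two timestamps the trial needs anyway (start of ventilation and randomisation). Eligibility, sample size and treatment content are unchanged. Two limits remain. Eligibility and deadline still end together, so a patient enrolled late in the window, or on a Friday evening, has little or no usable time; the second report makes this visible but does not remove it. Patients ventilated before ICU admission would face a stricter deadline than under the present outcome section.

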### Secondary outcomes

The schedule of outcome assessments is detailed in table 2.

**Table 2 T2:** Schedule of assessments

	Randomisation	Day 1	Day 3	Day 7	Awakening	Weekly	ICU discharge	Hospital discharge	3 months posthospital discharge
Demographic data	X								
Muscle assessment									
Medicial Research Council sum-score (MRCss)^60 61^					X	X	X	X	
Grip strength^62^					X	X	X	X	
Physical function									
CPAx^63^		X	X	X	X	X	X		
ICU mobility^64^		X	X	X	X	X	X		
PFITs^59^					X	X	X		
Timed-Up and Go							X	X	X
Clinical Frailty Score^69^		(X)					X	X	X
Barthel Index		(X)					X	X	X
6 min Walk Test^70^								X	X
Health Related Quality of LIfe (HRQL)									
WHODAS 2.0^71^									X
HADS^72 73^									X
EQ-5D-5L^74^									X
Impact of Event Scale^75^									X
Health Economic Evaluation (CSRI)*									X

CPAx, Chelsea Critical Care Physical Assessment Tool; CSRI, Client Service Receipt Inventory; EQ-5D-5L, Euroqol-5 Dimension-5 Level; HADS, Hospital Anxiety and Depression Scale; ICU, intensive care unit; PFITs, Physical Function ICU Test–scored; WHODAS 2.0, WHO Disability Assessment Schedule 2.

### Strength and function

We will measure the Physical Function ICU Test–scored (PFITs) at awakening as described by De Jonghe *et al*^56^ then weekly within ICU and on ICU discharge.^57^ PFITs is a reliable and valid four-item scale (arm strength, leg strength, ability to stand and step cadence), with a score range of 0–10 and is responsive to change and predictive of key outcomes.^58^ Medical Research Council Manual Muscle Test Sum Score (MRC-ss)^59 60^ and handheld dynamometry^61^ will be measured on awakening, weekly, on ICU discharge and hospital discharge. Chelsea Critical Care Physical Assessment Tool (CPAx)^62^ and ICU Mobility Scale^63^ will be assessed three times during the first week within ICU, on awakening, weekly thereafter within the ICU and at ICU discharge. Timed Up and Go,^64 65^ Clinical Frailty Score (CFS)^66–68^ and Barthel Index will be assessed at ICU discharge, hospital discharge and 3 months posthospital discharge. Preadmission Barthel Index and CFS will be assessed by proxy on admission from family member or next of kin. Six-minute walk test^69^ will be performed, in accordance with American Thoracic Society guidelines, at hospital discharge and 3 months posthospital discharge.

### Health-related quality of life (QOL) outcomes

The following will be measured at 3 months posthospital discharge : WHODAS 2.0,^70^ Hospital Anxiety and Depression Scale score,^71 72^ Euroqol-5 Dimension-5 Level (EQ-5D-5L),^73^ Impact of Event Score^74^ and Client Service Receipt Inventory questionnaire, designed for this study to evaluate costs that fall on patients and their carers. Resource use and costs including direct intervention costs of therapists and equipment and general hospital costs (per bed day) will be recorded for each patient.

### Health economic substudy

We will also conduct an embedded health economic study to identify and define data collection for a future RCT where a full cost-effectiveness analysis (CEA) can be conducted. Within the feasibility study, we aim to address the following:

What the quality of the data and what potential problems are there for reporting QoL (EQ-5D-5L), resource use and costs.The cost implications of the proposed intervention in terms of impact for the NHS (inpatient stay bed days) and identifying the main cost drivers.Is the EQ-5D-5L appropriate for use in the future RCT?

The economic outcomes will include secondary care resource use within hospitals during inpatient stay, primary care resource use following discharge up to 3 months and resource use related to providing the intervention. The results will be reported in the form of descriptive statistics and will be used to inform a future CEA within a definitive RCT.

### Additional data collection

We will collect baseline data including demographic information, Functional Comorbidity Index, ICU diagnosis, APACHE II score, ventilation duration, ventilator-free days, ICU and hospital length of stay, within ICU drug history and duration and type of usual care physiotherapy.

### Implementation evaluation

We aim to investigate whether the protocolised early rehabilitation programme used in one NHS institution is transferable, as an RCT, into other similar NHS institutions. The design of a future multicentre study will be informed by identified facilitators and barriers to implementation. Implementation assessment will be based on the measures described by Proctor.^75^ A cross section of ICU staff and patients will be interviewed and complete questionnaires at trial completion to identify barriers impacting delivery of the study. Understanding of the integration and sustainability of the intervention are necessary to inform the design of a powered RCT. Acceptability will be measured at the beginning and end of the study from investigators and clinical staff by direct discussions and questionnaire. Our experience informs us that the introduction of this intervention is dependent on a cultural change within any unit for a proactive focus on early mobilisation. We aim to explore measures to help optimise implementation. Adoption, feasibility and fidelity measures will be monitored during the study by regular meetings with the investigators. Patient screening logs will identify the number of patients eligible for the study and barriers to enrolment. We will assess the degree to which it is possible to separate the staff caring for the intervention group from those caring for the patients in the control group.

We will report whether trial participation has influenced usual care within the participating units by prestudy and poststudy audits. Participating sites will collect data regarding number and seniority of therapy staff with dedicated time to work within the ICU; delirium and sedation protocols used; time, type and frequency of rehabilitation interventions delivered, who delivers the interventions and reasons why usual care may not be delivered.

The feasibility outcomes described earlier will be used to power a larger RCT.

